## Background

Lower back pain (LBP), in any of its forms (acute, subacute, chronic), is one of the principal reasons for consulting the general practitioner (GP). The annual prevalence of LBP is estimated at 14.8% in a study carried out in the Spanish population [1], and these results were confirmed by the 2006 Spanish National health survey [2] and recent data from the Primary Care Information System of Catalonia [3].

LBP has an important impact in the performance of daily tasks and the quality of life of the individuals affected by this pathology. It also has social and family repercussions which are often ignored [1,4]. LBP is one of the six most frequent health problems in developed countries [5,6]. When the LBP diagnosis is established, the minimisation of disability and the cost of labour absenteeism constitutes a shared problem among patients, health professionals, business management, and administration, and makes early intervention necessary to avoid chronic LBP. Some epidemiological studies show that aspects such as psychosocial malaise and fear and avoidance behaviour are associated with a higher risk of developing incapacity in the long term. In patients with these characteristics, a cognitive behavioural intervention has been shown to be effective in reducing this risk [7,8]. Therefore, psychological and social factors associated with the symptoms should be considered because they could affect the level of pain and increase the risk of evolution to chronic LBP [9-12]. Failure to reduce pain represents an important increase in the economic cost to society and reduction in the quality of life of the patient [13,14].

The labour absenteeism caused by LBP is estimated at an average of 21.9 working days lost per illness episode, which represents a cost of 1260 € per worker per year [3]. This cost would be higher if the calculation also took into account "presenteeism" (reduced work productivity), which doubles or triples the cost of labour absenteeism alone [15]. Clinical practice guidelines include scant information about the cost-effectiveness of the treatments, except for those provided by the National Institute for Health and Clinical Excellence (NICE) [16]. In addition, the few studies published have important methodological limitations and are very heterogeneous, which limits the available evidence about the cost effectiveness of LBP interventions [17,18].

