##### Other variables

The main independent variable is the intervention arm: MBEGI, or usual clinical care.

Sociodemographic and clinical variables were detailed in the study protocol [21]. Among others, clinical variables are PHCC and hospital emergency visits due to current sub-acute LBP episode; patient compliance with recommendations and treatments; prescribed diagnostic tests; prescribed pharmacological treatment; referrals to other departments; and nonpharmacological treatment measures [41]. Absenteeism will be calculated, and reduced work productivity (presenteeism) will be measured by the Quantity and Quality instrument (QQ). The amount and quality of productivity will be measured on a 10-point numerical rating scale, with 0 representing "nothing" and "very poor quality," respectively, and 10 representing "normal quantity" and "normal quality," respectively [42,43].

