##### Other non-pharmacological therapeutic measures and Patient Compliance

The non-pharmacological therapeutic measures are detailed in Table 4.

**Table 4 T4:** Measurements of cost

Measurements of costs					
**Type of cost**	**Costs for**	**Specification**	**Source of resources used**	**Source of costs per 'unit'**	**Cost calculation**

Medical direct costs	Primary Health Care consultations	General Practitioner Practice nurse Physiotherapist Psychologists	Self-reported and comparison the answers by E-cap (electronical clinical records e-cap)	Catalan Institute of Health provider	Number of visits × tariff
	
	Secondary care consultations	Other specialists	Self-reported and comparison by E-cap	Catalan Institute of Health provider	Number of visits × tariff
	
	diagnostic tests	Radiology, magnetic resonance, scanner, electromyogram	Self-reported and comparison by E-cap	Catalan Institute of Health provider	Tests done × tariff
	
	Pharmaceutical treatment	muscle relaxants, analgesics, NSAIDs, corticoids, anxiolytic, Antidepressants and gastric protectors	Self-reported and comparison by E-cap	Standard Pharmaceutical Prices by Consejo General de Colegios Oficiales de Farmacéuticos	Medicines bought × price medicine
	
	Additional medical services	Traumatology, rehabilitation, neurosurgery, other therapies	Self-reported and comparison by E-cap	Catalan Institute of Health provider	Services provided × tariff
	
	Material provided in intervention	leaflet, booklet, CD, DVD	Provider	Provider; production costs	Number of material × price per material
	
	Material used in intervention	mat, postural stool, tennis ball	Provider	Provider; market price	Number of material × price per material

Non medical direct costs	Aid to patients who face disabilities	Aid in household, aid for young children	Self-reported	Patient	hours of aid × price per aid
	
	Additional therapies	Gymnasium, swimming, Yoga/Tai Chi/stretching, other	Self-reported	Patient	Number of months × price per month
		
		Acupuncture, osteopathy, massage, homeopathy, other therapies	Self-reported	Patient	Number of sessions × price per session

Indirect costs	Cost of lost productivity	Absenteeism	Self-reported and comparison by E-cap	Self-reported, profession classification assigned according to Spanish National Institute of Statistics	Days of work sick leave × salary

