		Presenteeism	Self-reported	Self-reported, profession classification assigned according to Spanish National Institute of Statistics	reduction percentage × productivity

During follow-up visits (at 3, 6 and 12 months) we will ask the patient about compliance with treatment recommendations and data collection questionnaires will be completed.

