To adjust comparisons and to account for cluster randomisation, multilevel linear regression analyses on repeated measures on each of the outcome scales will be used to assess the effect of intervention and to investigate the factors that influence each of the outcome scales at each time point. The possible association between intervention and time will be studied. The PHCC and the individual will be considered as random effects and intervention and time as fixed effects.

The incremental cost-effectiveness ratios were calculated as the difference in mean costs between the MBEGI and the usual care divided by the difference in mean effect, measured in natural unit, between MBEGI and the usual care.

Utilities will be calculated from the SF-12 scores with the corresponding Oxford University algorithm. The QALY will be calculated using these utilities, adjusted by time. The incremental cost-utility ratio will be calculated by dividing the difference in mean total costs between the MBEGI and the usual care by the difference in QALYs [56,57].

To determine the uncertainty surrounding these ratios, 95% confidence intervals for cost-effectiveness ratios will be calculated by the non-parametric bootstrap method [51].

Acceptability curves will be use to determine the probability that the MBEGI will be cost effective compared with usual clinical care at different values of the maximum acceptable ratio.

A deterministic sensitivity analysis will be performed to assess the robustness of the results [58]. The sickness days, GP visits and the number of medications will be measured to assess the impact on costs and cost-effectiveness. The discount rate will be 1% and 5%.

Confidence intervals around point estimates will be reported. The results will be presented in a disaggregated as well as aggregated form.

The significance level of all models will be set at 5%. The SPSS statistical package for Windows, version 19 (SPSS Inc., Chicago, IL) and the Stata/SE version 11·1 for Windows (StataCorp LP) will be used for statistical analysis.

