Despite the 1-year time horizon, our study includes data from more than a natural year, so the possible effect of inflation could slightly modify the prices and values of the different variables. To minimise these effects, we will convert costs and benefits obtained in different years to a base year: the year with the most recently published price levels. In addition, a 3% rate will be applied, which is closest to the actual discount rate.

Another point to consider in the costs estimation is the possible influence of the current economic situation. A review by Degenais et al. [17] showed that the major part of costs derived from LBP are indirect, resulting from the sick leave factor, which has a very important weight in the equation. In addition, due to the current labour uncertainty in our context, workers are more hesitant to request sick leave, which could contribute to underestimation of costs. We will attempt to minimise this impact by including the concept of workforce presenteeism and by the sensitivity analysis.

We also cannot discard the possible effect on costs estimation of the high unemployment rates related to the current economic crisis. Nonetheless, it can be assumed that the level of unemployment would be similar in both study groups, which then would not affect the cost-utility and cost-effectiveness results.

If the intervention is shown to be cost-effective and utility-cost, it could be applied to the primary care population with the expectation of the following results:

■ decreased intensity of LBP

■ decreased duration of the episode and recurrent LBP

■ improved quality of life

■ decreased incidence of chronic LBP

■ decreased days of labour absenteeism and presenteeism

■ reduced pharmacy costs

■ reduced costs to the National Health System in the provision of services due to this pathology

■ Reduced social costs to the patient and his/her family

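### The deterministic sensitivity analysis leaves out presenteeism, which the protocol's own background figure puts at half or more of productivity cost

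*Protocol article*

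**What the plan says.** The Background gives absenteeism as "an average of 21.9 working days lost per illness episode", "which represents a cost of 1260 € per worker per year", and says that this cost would be higher with presenteeism, "which doubles or triples the cost of labour absenteeism alone". The Discussion highlights the inclusion of presenteeism and says that it appears to matter for the cost of low back pain.

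Presenteeism is measured with the Quantity and Quality (QQ) instrument. Under Other variables: "The amount and quality of productivity will be measured on a 10-point numerical rating scale". Table 4 costs absenteeism as "Days of work sick leave × salary" and presenteeism as "reduction percentage × productivity". In the same table, absenteeism is self-reported and checked against the electronic record, while presenteeism is self-reported only.

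For the deterministic sensitivity analysis, Statistical Analysis states: "The sickness days, GP visits and the number of medications will be measured to assess the impact on costs and cost-effectiveness". It adds discount rates of 1% and 5%. No other parameter is named.

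On sick leave that may be under-used in the current economic climate, the Discussion says: "We will attempt to minimise this impact by including the concept of workforce presenteeism and by the sensitivity analysis".

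**The concern.** A deterministic sensitivity analysis is meant to show whether the conclusion survives changes in inputs that are both large and uncertain. By the protocol's own account presenteeism is large. It is also less secure than the other productivity component, since it rests on two self-ratings without a check against records and has to be turned into money by a valuation rule. The listed parameters do not touch it. The analysis could therefore be carried out exactly as written and the result called robust, although about half to two thirds of productivity cost was never varied. A reader of a societal-perspective evaluation would reasonably assume that such a statement covered it.

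The Table 4 cell adds to this in a smaller way. It shows neither the working time over which a percentage loss applies nor how two scores become one percentage. The valuation that needs testing is thus not fully written down.

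**Working it through.** **Inputs.** From the Background: absenteeism EUR 1,260 per worker per year, 21.9 working days per episode, and a multiplier k of 2 to 3 when presenteeism is added. The multiplier is a cited literature value and cannot be rebuilt from the article, so it is taken as given.

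**1. Share of productivity cost.** With k = (absenteeism + presenteeism) / absenteeism, the presenteeism share is (k − 1)/k.
- k = 2: total 2 × 1,260 = EUR 2,520, presenteeism EUR 1,260, share 1/2 = 50%.
- k = 3: total 3 × 1,260 = EUR 3,780, presenteeism EUR 2,520, share 2/3 = 67%.
- If the sentence instead means that presenteeism alone costs two to three times absenteeism, the shares are 2/3 = 67% and 3/4 = 75%.

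On the lower bound presenteeism ties with absenteeism. Above it, presenteeism is the larger.

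**2. Leverage of a tested and an untested input.** A 20% change is assumed for both, only to compare them. Productivity cost moves by 0.20 × 1/k for sick days and by 0.20 × (k − 1)/k for presenteeism.

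| | k = 2 | k = 3 |
|---|---|---|
| Sick days ±20% (tested) | 10% | 6.7% |
| Presenteeism ±20% (not tested) | 10% | 13.3% |

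**3. Effect of the scoring rule.** Illustrative scores, with reduction percentages under three possible rules:

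| Quantity, quality | Quantity only | Mean of the two | Product |
|---|---|---|---|
| 8, 8 | 1 − 0.8 = 20% | 1 − 16/20 = 20% | 1 − 0.64 = 36% |
| 7, 8 | 1 − 0.7 = 30% | 1 − 15/20 = 25% | 1 − 0.56 = 44% |

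For scores of 8 and 8 the rules differ by a factor of 36/20 = 1.8. At 1,260/21.9 = EUR 57.5 per day (assuming one episode a year), that is EUR 12 against EUR 21 for one affected day, and EUR 690 against EUR 1,243 for 60 days. The number of affected days is an assumption. These are costs per person in one arm, not differences between arms.

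**4. Effect on the ratios.** The numerator of each ratio is ΔC = ΔA + ΔP + ΔO, where A is absenteeism, P presenteeism and O all other cost. Excluding presenteeism changes the numerator by ΔP, and a different scoring rule changes ΔP itself. The article gives no figure for ΔP, so the shift in the ratios cannot be computed.

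**5. Other stated analyses.** The bootstrap intervals and acceptability curves carry patient-to-patient sampling variation in presenteeism cost, but every replicate uses the same valuation rule. Reporting results in disaggregated form would show the component, but not the ratios under another valuation.

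**The case against.** **Largest driver of the result.** A reader might infer that presenteeism is the main driver of incremental cost. The document does not support that. The multiplier is a background literature figure, not a forecast for this trial. The Discussion attributes most of the cost of low back pain to indirect cost arising from sick leave, and sick days are varied. A cost that is similar in both arms cancels in the numerator, however large its level. This objection stands, and the point is confined to the share of productivity cost.

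**A broken promise in the Discussion.** A reader might also infer that the Discussion commits to varying presenteeism. It does not. It names two separate remedies for under-recorded sick leave: including presenteeism, and the sensitivity analysis, which varies the very quantity feared to be under-recorded. There is no contradiction, only an input relied upon and left untested.

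**An unusable formula or double counting.** The Table 4 entry is largely shorthand. Productivity can be read as the value of output over a period, the wage source is given in the same row, and other cells are equally terse. Scoring is referred to cited sources. Presenteeism is also defined as reduced output during work actually performed, so sick-leave days already fall outside it. This largely stands, and the formula is therefore only a secondary clarification.

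**Assumed inputs.** The euro illustrations depend on assumed scores and days and do not measure any error in the plan. They show only that the valuation rule matters.

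What the objections do not remove is that the article prints an explicit parameter list and presenteeism is not on it.

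**Conclusion.** The point holds in a limited form. On the protocol's own figure, presenteeism is about 50% to 67% of productivity cost (67% to 75% on the other reading of the sentence), which makes it the largest or joint-largest productivity component. It is also the one whose valuation is least secure. The stated deterministic sensitivity analysis does not vary it, so a conclusion of robustness would not extend to it. The shares rest on the literature multiplier quoted in the Background, and the comparison with sick days rests on an assumed equal 20% change. The size and direction of any effect on the incremental ratios are unknown. This is a worthwhile and inexpensive improvement to a stated analysis, not a defect that invalidates the evaluation.

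**What to change.** In Statistical Analysis, add presenteeism to the deterministic sensitivity analysis with at least two scenarios:
- (a) presenteeism cost excluded;
- (b) either an alternative valuation of the QQ scores, for example the quantity score alone, or a percentage variation stated in advance.

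Report the incremental cost-effectiveness and cost-utility ratios under each. The existing parameters and the discount-rate runs can stay.

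As a secondary clarification, expand the presenteeism cell of Table 4 to show the working time used (time at work in each interval between assessments, excluding sick-leave days) and the pre-specified rule for combining the two scores. Several rules are defensible. What matters is that one is fixed before the analysis.

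The scenarios cost a few extra runs on data already collected. The article does not list time at work as a separate item. If it is not recorded, the clarification also needs a stated assumption about normal working days, from which recorded sick leave is subtracted.

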##### Ethical aspects

The study will be conducted according to Guidelines of the Helsinki Declaration and of Good Clinical Research Practice. The project/study protocol has been approved by the Ethical and Clinical Research Committee of IDIAP Jordi Gol, Institute of Research in Primary Health Care.

This trial is registered as Current Controlled Trials (ISRCTN58719694)

More details of the intervention, of patient adherence to the intervention and to non-pharmacological treatment, and the analysis of effectiveness have been published in the protocol for analysis of the effectiveness of the intervention [21].

## Discussion

With this study, we hope to contribute evidence about the cost-effectiveness and cost-utility of MBEGI in reducing episodes of non-specific LBP and the associated social and health costs. This evidence could help health professionals and administrators to make more efficient decisions to address this problem in the primary care setting.

A review of the literature found very few studies of cost-effectiveness and cost-utility related to LBP, and that considered the societal perspective and used a rigorous methodology and a broad sample [59]. On the other hand, the recent review by Catalá-López et al. points out the lack of economic assessment in Spain with respect to musculoskeletal care [60]. The cost-effectiveness and cost-utility analysis of MBEGI proposed in this study, which incorporates most of the relevant costs of LBP, includes a follow-up period that will permit the identification of significant changes and the systematic description of the methods used, will facilitate the interpretation and comparison of the results.

A strength of the study is that the MBEGI has been designed as a pragmatic effectiveness trial. In this type of design, the interventions reflect what may happen in practice and the results are often more generalizable and hence preferable for economic evaluation [44,61].

Information about consumption of resources will be gathered in parallel with the collection of data about the effectiveness of the intervention; therefore, primary data will be obtained in terms of effectiveness and costs to inform the economic evaluation.

The analysis will adopt the social perspective; it is unusual to encounter economic evaluation studies with this perspective, even though LBP is a disease with an important impact on the daily life of the patient as well as the society. Nonetheless, the determination and collection of all of the costs and benefits to the patient, family members, and the National Health Service is a complex task. This study attempts to include the majority of all costs analysed in the studies reviewed. Nonetheless, some costs have been eliminated, such as those attributable to the primary care centre operations, since we could assume that there will be no relevant differences between the treatment and control group in this regard.

It is worth highlighting the inclusion of the concept of presenteeism in estimating labour costs. This concept has not often been applied in calculating the costs of LBP, and seems to have an important impact on those costs [15,62].

The fact that the direct costs of health care will be obtained from the most recent information published in the DOGC will mean that their allocation will be standardized.

We should also note that the participants will be are being recruited from PHCC. Although this aspect could affect the external validity of the study, the National Health Service in Spain provides universal free coverage. More than 70% of the general population visits a primary care centre at least once a year and this percentage increases if we consider longer time periods. In addition, given the size and heterogeneity of the sample and the high number of participating centres, we can assume that the study population represents the Spanish population with this problem, and therefore the results are potentially generalizable.

On the other hand, we have assumed that the usual care attention is to a certain extent homogeneous among the participating GP and nurses. Most of these professionals work for the Catalan Institute of Health and follow the recommendations of the "Clinical Practice Guidelines for lumbar column pathology in adults". Nonetheless, it is very probable that a certain variability exists in their application. In addition, the professionals who participate in research projects tend to be both motivated and more experienced. In any case, we assume that there may be variability, even though this would be similar in both arms of the study.

Another possible limitation is subjects lost to follow-up and/or the non-compliance rate, due to the long duration of the fieldwork. Efforts will be made to minimize these losses with the use of reminders (telephone calls, text messages, and the 6-month interview) that facilitate follow-up and compliance, along with the empathy and communication skills of the interviewers who will be doing the fieldwork.

Despite the 1-year time horizon, our study includes data from more than a natural year, so the possible effect of inflation could slightly modify the prices and values of the different variables. To minimise these effects, we will convert costs and benefits obtained in different years to a base year: the year with the most recently published price levels. In addition, a 3% rate will be applied, which is closest to the actual discount rate.

Another point to consider in the costs estimation is the possible influence of the current economic situation. A review by Degenais et al. [17] showed that the major part of costs derived from LBP are indirect, resulting from the sick leave factor, which has a very important weight in the equation. In addition, due to the current labour uncertainty in our context, workers are more hesitant to request sick leave, which could contribute to underestimation of costs. We will attempt to minimise this impact by including the concept of workforce presenteeism and by the sensitivity analysis.

We also cannot discard the possible effect on costs estimation of the high unemployment rates related to the current economic crisis. Nonetheless, it can be assumed that the level of unemployment would be similar in both study groups, which then would not affect the cost-utility and cost-effectiveness results.

If the intervention is shown to be cost-effective and utility-cost, it could be applied to the primary care population with the expectation of the following results:

■ decreased intensity of LBP

■ decreased duration of the episode and recurrent LBP

■ improved quality of life

■ decreased incidence of chronic LBP

■ decreased days of labour absenteeism and presenteeism

■ reduced pharmacy costs

■ reduced costs to the National Health System in the provision of services due to this pathology

■ Reduced social costs to the patient and his/her family
